### 2.6. Assignment of interventions

Stratified block randomization will be employed, and stratification will be based on the number of participants (<20 vs ≥20). Each cluster will be assigned to the intervention or control group based on a computer-generated random number table, which will be created by a biostatistician at the University of Tsukuba ([name]). It will be maintained by a researcher not associated with the research team at the Physical Fitness Research Institute, Meiji Yasuda Life Foundation of Health and Welfare. The allocation will be performed through central registration and disclosed to the participants and researchers via email. Due to the nature of the intervention, blinding was considered difficult to implement.

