### 1.2. Trial design

The proposed study is a 2-arm cluster-randomized controlled trial (cRCT) with a wait-list control group. After enrollment, each cluster (workplace) will be assigned to the intervention or control group in a 1:1 ratio using stratified block randomization. The effectiveness of the intervention program will be assessed by evaluating data from the intervention and control groups for the first 12 weeks at the employee level. The control group will not be provided with any program elements during this period. However, they will be provided with the program after the waiting period, and data from this program period will be used, along with data from the intervention group, for explanatory analyses.

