## 2. Methods

### 2.1. Participants

This study began in March 2024 in the Japanese workplace and will continue until March 2025. The eligibility criteria for employees are: (1) being aged ≥18 years and <65 years; and (2) being home-based teleworkers for at least 1 d/wk. The exclusion criteria for employees are: (1) being prohibited from exercising by their doctors; (2) planning long-term business trips or retirement during the study; (3) being pregnant or possibly pregnant; and (4) being judged by the research director to be inappropriate for inclusion, for example, not agreeing to return the measuring instruments. Recruitment will be conducted through the research team’s network of companies that employ teleworkers. The employee coordinator of the company that agrees to participate will send invitations to employees who meet the eligibility criteria. Based on the employees who agree to participate at this stage, clusters of 20 to 100 participants will be selected and allocated to units, such as departments and offices, where contamination does not occur. Subsequently, participants will receive baseline survey instructions and instruments.

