	**STUDY PERIOD**						
	**Enrollment**	**Allocation**	**Post-allocation**				
**TIMEPOINT**	**March-July 2024**	**Immediately after enrollment**	**Baseline**		**3-month follow-up**		**6-month follow-up (only CG)**

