**ENROLLMENT:**							
**Eligibility screen**	X						
**Informed consent**	X						
**Allocation**		X					

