### 2.9. Ethics and dissemination

The study protocol was approved by the Ethical Committee of the Meiji Yasuda Life Foundation of Health and Welfare (approval no. 2023–0002) on February 6, 2024. The study will be conducted in accordance with the ethical standards of the World Medical Association’s Helsinki Declaration (1964, amended most recently in 2013), and informed consent will be obtained from all the participants according to the following procedure. If the company agrees to participate in the study, the company leader will invite employees who meet the eligibility criteria to participate. The investigation agency will mail a consent form to each employee, who will informally consent at the time of the baseline survey, and the participant will sign and return the form officially. A privacy concern specific to teleworkers is that home addresses are obtained to post instruments to those who do not come to the office. This point will be adequately explained to the participants, and their personal information will be strictly managed. The study results will be submitted and published in a peer-reviewed scientific journal. The research team plans to publish these results as a health management guide for teleworkers.

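### Table 1 schedules baseline after allocation, and nothing holds back the allocation email, so known allocation can influence the baseline step count used in the primary analysis

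*Protocol article*

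**What the plan says.** **Order of events.** Table 1 (section 2.4) gives allocation its own column, timed "Immediately after enrollment". The baseline column is the first one under the heading "Post-allocation", and the baseline mark for step count is in that column. Section 1.2 is compatible with this: "After enrollment, each cluster (workplace) will be assigned to the intervention or control group in a 1:1 ratio using stratified block randomization". It does not mention baseline.

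**Disclosure.** Section 2.6: "The allocation will be performed through central registration and disclosed to the participants and researchers via email". It gives no date for the email and no condition for sending it. It adds: "Due to the nature of the intervention, blinding was considered difficult to implement".

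**Use of baseline.** The primary outcome is the change in daily steps from baseline to the end of the intervention, measured by a waist accelerometer worn for 14 days (section 2.3.1). Measurement takes place in the two weeks before and the two weeks after the intervention (section 2.4). The primary GEE model has group as a factor and baseline steps as a covariate, and the listed secondary outcomes are analysed in the same way (section 2.8).

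**Consent.** Table 1 marks "Informed consent" in the enrollment column, before allocation. Section 2.9 describes employees "who will informally consent at the time of the baseline survey, and the participant will sign and return the form officially".

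**The concern.** Adjusting for baseline, or subtracting it, is safe only if allocation cannot have affected it. Here the baseline is two weeks of walking, which participants control. The intervention includes an individual and team step competition (section 2.2.2), while controls wait 12 weeks. Someone who knows the arm could start walking more early, or could hold back before the competition starts. The low back pain and work-environment questionnaires at baseline are open to the same influence.

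The resulting baseline difference would pass into the estimated treatment effect, and the data would not show whether it arose by chance or from knowledge of the arm.

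The consent conflict is a second, separate matter. If section 2.9 describes what happens, the formal decision to take part falls after allocation under Table 1's order, and refusal could differ between arms.

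**Working it through.** **1. The plan's own figures.** Section 2.5 uses a difference of 800 steps and an SD of 2400: 800/2400 = 0.33. It states 146 per group, 292 in total. The design effect is 1 + (20 - 1) x 0.02 = 1.38, and 292 x 1.38 = 402.96, so 403 as stated. With 80% completion, 403/0.80 = 503.75, against a stated 500. These figures reproduce closely and are not in dispute. The 800-step target is the yardstick below.

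**2. The sequence, side by side.**
- Table 1: enrollment, then allocation, then baseline.
- Section 1.2: enrollment, then assignment.
- Section 2.1: employees agree, clusters are formed, and then "Subsequently, participants will receive baseline survey instructions and instruments". This places the instruments after cluster formation. It does not say whether arms are known by then.
- Section 2.6: disclosure to participants, undated.

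Table 1 alone fixes baseline after allocation. No passage contradicts it, and none separates the date of disclosure from the date of allocation.

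**3. How a baseline shift reaches the estimate.** Let Y0 be baseline steps, Y1 follow-up steps, G the group and b the slope of Y1 on Y0. Then

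Y1 - Y0 = a + tau x G + (b - 1) x Y0

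is the same model as

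Y1 = a + tau x G + b x Y0.

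So tau is (difference in mean Y1) - b x (difference in mean Y0). Suppose knowledge of the arm adds D steps to the intervention arm's baseline relative to control and leaves follow-up unchanged:
- adjusted analysis: bias of about -b x D
- raw change score: bias of -D
- follow-up compared without the baseline covariate: no bias from this source

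If D is negative, the sign reverses and the effect is inflated.

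**4. Size, by assumption only.** The documents give neither b nor D. I assume b from 0.5 to 0.8 and D from 200 to 400 steps.
- Low end: 0.5 x 200 = 100 steps; 100/800 = 12.5%.
- High end: 0.8 x 400 = 320 steps; 320/800 = 40%.

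With the intervention arm's baseline raised, a true 800 would be estimated on average as 700 down to 480. With it lowered by the same amounts, the estimate would be 900 up to 1120.

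**5. Illustrative power in the unfavourable direction.** With 146 effective participants per arm and SD 2400, the standard error is 2400 x sqrt(2/146) = 281 steps. Power is about Phi(effect/281 - 1.96): 0.81 at 800, 0.70 at 700 and 0.40 at 480.

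**The case against.** **The email date is not stated.** Table 1 dates allocation, not disclosure, and a condensed article may omit when the email goes out. This stands as a limit. A reader might infer that participants do know their arm at baseline, but the documents only permit that. They do not say it. If the email was in fact held, one sentence saying so would settle the point. What remains is that the schedule as printed puts baseline after allocation with no safeguard.

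**Adjustment helps.** It is tempting to say that baseline enters twice, as subtrahend and as covariate, and that adjustment therefore makes matters worse. The algebra shows the opposite. Adjustment reduces the bias from D to b x D, a reduction of 20% to 50% for b of 0.8 to 0.5, and nothing is counted twice. It does not remove the bias.

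**Section 2.1 does not prove the order.** Its reference to allocating participants to units such as departments describes forming clusters, not assigning arms. It should not be cited as evidence that instruments follow randomisation.

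**Agreement comes first.** Under section 2.1 employees agree to take part before clusters are formed. A reader might infer the recruitment bias of cluster trials in which people are first approached after allocation. The text does not support that. What remains is possible refusal between initial agreement and the signed form.

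**Objective measurement and stated limitation.** An accelerometer removes reporting bias but not a change in walking. The Discussion lists nonblinding as a limitation in general terms, whereas this part of it can be avoided.

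**Conclusion.** The concern holds as a weakness in the order of procedures: followed as written, the plan lets known allocation affect the primary baseline and the baseline self-reports. The bias in the adjusted effect is about b x D, toward the null if the intervention arm's baseline rises relative to control and away from it if it falls. The figure of 12.5% to 40% of the target rests wholly on assumed b and D, a uniform shift and an unaffected follow-up. It shows what is possible and does not estimate what happened. The sample size is not affected.

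The conflict on consent timing between Table 1 and section 2.9 is real and needs reconciling. Its effect on selection is limited by the earlier agreement and cannot be sized from the documents.

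**What to change.** 1. Keep randomisation central, but release a cluster's allocation to participants and researchers only after its 14-day baseline wear, baseline questionnaire and signed consent forms are complete. State this in section 2.6.
2. In Table 1, move Baseline ahead of Allocation, or show disclosure as a separate step after Baseline. The consent row already precedes allocation and need not move.
3. Reword section 2.9 so that its consent timing agrees with Table 1.
4. Enrollment was scheduled for March to July 2024, so for some clusters the email may already have gone out. Report how many were told before baseline was complete. Where dates were recorded, add a sensitivity analysis that compares follow-up step count without the baseline covariate, or one that excludes those clusters if enough remain.

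**Cost.** The email goes out about two weeks later per cluster, with edits to one table and two sections. Section 2.4 already places baseline in the two weeks before the intervention, so that measurement period is not extended. The sensitivity analyses need disclosure and baseline dates by cluster, which the article does not show were kept. The follow-up-only comparison is also less precise. If baseline and follow-up variances are equal, so that b is the correlation, the residual variance is 1/(1 - b^2) times as large, ignoring clustering: 1/(1 - 0.25) = 1.33 at b = 0.5 and 1/(1 - 0.64) = 2.78 at b = 0.8. It should support the primary analysis, not replace it.

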### 2.7. Data collection and management

Self-reported data will be obtained using a web-based questionnaire, whereas objective data will be obtained using measuring instruments that will be sent to each participant. The researchers will ensure that the web-based questionnaire can be accessed from the participant’s personal computer, and easy-to-follow instructions will be attached to the measurement device. The survey period will be 2 weeks, and a reminder email will be sent to participants who do not respond. To protect the privacy of personal information, the researchers will outsource email distribution and instrumentation to an investigation agency that has signed a confidential disclosure agreement. The research team will not obtain the participants’ personal information. The investigation agency will maintain a strict list of the participants’ personal information and research IDs. The investigation agency (identified data) and the research team (de-identified data) will password-protect the data and store it on a secured computer. The final trial dataset will be accessible to the researchers on the study team. However, access will be strictly managed until the trial is completed.

### 2.8. Statistical methods

Efficacy will be analyzed using an intent-to-treat approach, regardless of adherence. The characteristics of the clusters and participants will be compared by group allocation using means (SDs) or medians (interquartile ranges) for continuous variables, and counts and percentages for nominal variables. The primary outcome, which is the change in daily step count between baseline and the end of the intervention, will be analyzed using generalized estimating equations (GEEs) to adjust for clustering. The GEE method will employ an exchangeable correlation structure and an identity link with a normal distribution. The mean model will include the allocated group as a factor and baseline step count as a covariate. We will analyze secondary outcomes (PA measures, LBP scale, and work environment scale) using the same method. A sensitivity analysis will be conducted for the primary outcome based on the per protocol set. All statistical tests will be 2-sided with a 5% significance level.

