**Methods:**

This cluster randomized trial will have a target sample size of 500 participants. The target population is healthy adults aged 18-64 years who telework at least once per week. Randomization will be conducted on a stratified block basis for clusters of 20 to 100 individuals within the recruited companies. The intervention period will be 12 weeks and comprise individual (online lectures, feedback, and periodic email messages), sociocultural (team building through step competition), physical (poster and tabletop pop-up), and organizational (encouraging message from an executive) strategies. The intervention group will be compared with a wait-list control group. The primary outcome will be the number of steps taken, as assessed by an accelerometer, and the secondary outcomes will be musculoskeletal pain and a telecommuting environment. The study protocol was registered with the University Hospital Medical Information Network Clinical Trials Registry (ID: UMIN000053861) (https://center6.umin.ac.jp/cgi-open-bin/ctr/ctr.cgi?function=brows&action=brows&recptno=R000061478&type=summary&language=J).

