### 2.5. Sample size

The effect size of the intervention program regarding the primary outcome, a change in step count over 12 weeks, was estimated with Cohen *d* = 0.33. This is based on a previous study,^14^ with an SD of 2400 and an estimated difference between groups of 800 in the expected increase in step count. An increase of 800 steps is also a clinically meaningful difference.^38^ The calculation was performed with a type 1 error rate of 0.05 and a statistical power of 0.80, and the required sample size was estimated at 146 in each group for a total of 292 participants. To consider the design effect as a cRCT, the average number of cluster sizes was assumed to be 20, the intraclass correlation coefficient was 0.02, and the number of participants was calculated to be 403. Additionally, we estimated that 80% of the participants would finish the intervention; therefore, a total of 500 participants would be recruited. To improve the participation rate, some of the workplace-based results will be fed back to the employee coordinator in charge of each cluster for their health promotion strategies after the study is completed.

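### The GEE mean model leaves out the size stratum used in randomisation, so the reported standard error may be too large if step change differs between strata

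*Protocol article*

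**What the plan says.** Section 1.2 describes the allocation: "each cluster (workplace) will be assigned to the intervention or control group in a 1:1 ratio using stratified block randomization". Section 2.6 names the one stratification factor: "stratification will be based on the number of participants (<20 vs ≥20". Section 2.8 specifies the primary analysis of step change. On the correlation structure, link and distribution it states: "The GEE method will employ an exchangeable correlation structure and an identity link with a normal distribution". On the terms it states: "The mean model will include the allocated group as a factor and baseline step count as a covariate". The same method is carried to the secondary outcomes. No stratum term is named.

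Two other statements decide whether the stratum can vary at all. The Abstract says "Randomization will be conducted on a stratified block basis for clusters of 20 to 100 individuals within the recruited companies", and section 2.1 says "clusters of 20 to 100 participants will be selected and allocated to units, such as departments and offices, where contamination does not occur". Section 2.5 sizes the trial on an average cluster of 20.

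**The concern.** Stratified randomisation balances the arms on the stratum. An analysis earns the benefit of that balance only if the stratum is in the model. If it is left out and the strata differ in mean step change, that difference stays in the residual between-cluster variation. The reported standard error then exceeds the true spread of the estimate, and the test rejects less often than it should under both the null and the alternative. With about 25 clusters (500/20), or fewer if clusters are larger, between-cluster variation matters, so some power could be lost for want of one model term. Section 2.8 lists the model terms explicitly, so this is a stated choice and not a detail left open.

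**Working it through.** **Inputs from the documents.** SD 2400 and difference 800 steps (section 2.5: "with an SD of 2400 and an estimated difference between groups of 800 in the expected increase in step count"), d = 0.33, two-sided 5% level, power 0.80, ICC 0.02, average cluster 20, 80% completion, 500 recruited.

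**The plan's own figures.** At d = 0.33 the normal formula gives 145 per arm; the t-based value is 145.1, which rounds up to the stated 146 (292 in total). Design effect: 1 + 19 × 0.02 = 1.38, and 292 × 1.38 = 402.96, so 403. Completion: 403/0.80 = 503.75, against the stated 500. The sample size reproduces closely and makes no use of the stratum.

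**Can the stratum vary?** If all clusters have 20 to 100 participants, every cluster falls in the upper stratum. The stratum column is then constant and collinear with the intercept: the design matrix is singular, and the gain is exactly zero. Against that, an average of 20 with a minimum of 20 would need every cluster to be exactly 20, and section 2.6 creates a stratum below 20. Sections 2.5 and 2.6 therefore suggest that smaller clusters are expected, while the Abstract and section 2.1 exclude them.

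**If small clusters are enrolled.** The simulation used 24 clusters with 16 completers each (20 × 0.80), allocation balanced within strata, 20,000 replicates, and a t test on cluster means.

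- Variance of a cluster mean: 2400² × (0.02 + 0.98/16) = 468,000.
- True SE of the arm difference: √(468,000 × (1/12 + 1/12)) = √78,000 = 279 steps. The simulated spread was about 280 in every scenario, with or without the term.
- With half the clusters small and a stratum difference δ, the expected squared SE without the term is (468,000 + 24 × 0.25 × δ²/22)/6. For δ = 400 this is (468,000 + 43,636)/6 = 85,273, SE 292. For δ = 800 it is (468,000 + 174,545)/6 = 107,091, SE 327. Simulated mean SEs are slightly lower, as a mean of square roots must be.

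Results with 12 of 24 clusters small (without / with the term; SE from the runs with no treatment effect, power for a true effect of 800 steps):

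| Stratum difference δ (assumed) | Mean reported SE | Type I error | Power |
|---|---|---|---|
| 0 | 276 / 275 | 0.052 / 0.053 | 0.780 / 0.782 |
| 200 | 280 / 276 | 0.052 / 0.048 | 0.776 / 0.784 |
| 400 | 289 / 276 | 0.043 / 0.047 | 0.750 / 0.776 |
| 800 | 324 / 276 | 0.024 / 0.052 | 0.672 / 0.778 |

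With only 4 of 24 clusters small, power without / with the term was 0.786 / 0.778, 0.772 / 0.779, 0.768 / 0.778 and 0.718 / 0.777. The Monte Carlo standard error is √(0.78 × 0.22/20,000) = 0.003 per entry, and the two models were run on separate draws, so gaps of about 0.008 or less are within noise.

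**How large is δ?** The between-cluster SD implied by ICC 0.02 is 2400 × √0.02 = 339 steps (variance 115,200). With half the clusters small, δ adds δ²/4 to this. For δ = 400 the overall ICC becomes (115,200 + 40,000)/(5,760,000 + 40,000) = 0.027. For δ = 800 it becomes (115,200 + 160,000)/(5,760,000 + 160,000) = 0.046, more than twice the planning value.

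**Limits.** The simulation uses a model-based variance, equal numbers of completers in both strata and no baseline covariate. It is not a GEE with a robust variance. It shows direction and rough size only.

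**The case against.** The strongest objection is that, on the documented range of 20 to 100, the omitted factor is a constant, so nothing is lost and the real defect is the mismatched cut. This stands as far as it goes: the gain is zero in that case. It does not settle the matter, because the average of 20 and the stratum below 20 both point to smaller clusters.

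Second, the cost may outweigh the gain. With clusters averaging 40, 500 participants give about 12 clusters. Going from 10 to 9 degrees of freedom moves the t critical value from 2.228 to 2.262, and (2.262/2.228)² = 1.03, about 3% in squared interval width. This stands for a trial with few, large clusters; at 24 clusters no power loss beyond simulation noise appeared.

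Third, the benefit needs step change to differ by cluster size, and the documents say nothing about that. This also stands.

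A reader might infer that the analysis ignores the design. It does not: the exchangeable GEE handles clustering, which is the main design feature, and type I error without the term was 0.024 to 0.052. A reader might also infer a cut in the true variance from [1 + (m−1) × ICC × (1−r)]/[1 + (m−1) × ICC], where size explains a share r of between-cluster variance. Taking r from 0.10 to 0.25, m of 20 or 40 and ICC of 0.02 or 0.05 gives 3% to 17%. The documents support neither r, nor m = 40, nor ICC 0.05. Under balanced stratified allocation the true spread does not change anyway; only the reported standard error does.

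**Conclusion.** The point holds as a modest one that is worth fixing. The factor used to randomise is missing from a mean model whose terms are stated in full. The consequence is a possibly overstated standard error and a conservative test, with neither bias nor a raised false-positive rate from this omission. Its size depends on two things that the documents do not give: whether clusters below 20 are enrolled, and how far step change differs between strata.

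- No clusters below 20: no effect.
- Half the clusters small, difference up to 200 steps: power loss of about 1 point or less.
- Half small, 400 steps: about 3 points.
- Half small, 800 steps: about 11 points. This difference equals the whole planned treatment effect and is more than twice the between-cluster SD of 339 steps, so it is an upper extreme.

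A reader might infer that the term would also guard against chance imbalance in cluster size. A two-level term cannot correct differences between clusters of, say, 20 and 100, which share a stratum.

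**What to change.** First, reconcile the cut in section 2.6 with the 20 to 100 range in the Abstract and section 2.1, and with the average of 20 in section 2.5. State whether clusters below 20 are admitted, and what strata the allocation list actually used.

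Then add that stratum as a fixed term in the GEE mean model of section 2.8, for the primary and secondary outcomes. If it turns out that all randomised clusters lie in one stratum, say so and leave the model as it is. Settle this before outcome data are analysed.

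The cost is one line in the model statement, using data already held, and one cluster-level degree of freedom. That is small at about 25 clusters. It matters more if clusters are larger and fewer: at the extreme of 100 each, 500 participants give only 5 clusters.
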